## Abstract

**Background:**

Adherence to oral anticancer treatments is critical in the disease trajectory of patients with breast cancer. Given the impact of nonadherence on clinical outcomes and the associated economic burden for the health care system, finding ways to increase treatment adherence is particularly relevant.

**Objective:**

The primary end point is to evaluate the effectiveness of a decision support system (DSS) and a machine learning web application in promoting adherence to oral anticancer treatments among patients with metastatic breast cancer. The secondary end point is to collect a set of new physical, psychological, social, behavioral, and quality of life predictive variables that could be used to refine the preliminary version of the machine learning model to predict patients’ adherence behavior.

**Methods:**

This prospective, randomized controlled study is nested in a large-scale international project named “Enhancing therapy adherence among metastatic breast cancer patients” (Pfizer 65080791), aimed to develop a predictive model of nonadherence and associated DSS and guidelines to foster patients’ engagement and therapy adherence. A web-based DSS named TREAT (treatment adherence support) was developed using a patient-driven approach, with 4 sections, that is, Section A: Metastatic Breast Cancer; Section B: Adherence to Cancer Therapies; Section C: Promoting Adherence; and Section D: My Adherence Diary. Moreover, a machine learning–based web application was developed to predict patients' risk factors of adherence to anticancer treatment, specifically pertaining to physical status and comorbid conditions, as well as short and long-term side effects. Overall, 100 patients consecutively admitted at the European Institute of Oncology (IEO) at the Division of Medical Senology will be enrolled; 50 patients with metastatic breast cancer will be exposed to the DSS and machine learning web application for 3 months (experimental group), and 50 patients will not be exposed to the intervention (control group). Each participant will fill a weekly medication diary and a set of standardized self-reports evaluating psychological and quality of life variables (Adherence Attitude Inventory, Beck Depression Inventory-II, Brief Pain Inventory, 13-item Sense of Coherence scale, Brief Italian version of Cancer Behavior Inventory, European Organization for Research and Treatment of Cancer Quality of Life 23-item Breast Cancer-specific Questionnaire, European Organization for Research and Treatment of Cancer Quality of Life Questionnaire, 8-item Morisky Medication Adherence Scale, State-Trait Anxiety Inventory forms I and II, Big Five Inventory, and visual analogue scales evaluating risk perception). The 3 assessment time points are T0 (baseline), T1 (1 month), T2 (2 months), and T3 (3 months). This study was approved by the IEO ethics committee (R1786/22-IEO 1907).

**Results:**

The recruitment process started in May 2023 and is expected to conclude on December 2023.

**Conclusions:**

The contribution of machine learning techniques through risk-predictive models integrated into DSS will enable medication adherence by patients with cancer.

**Trial Registration:**

ClinicalTrials.gov NCT06161181; https://clinicaltrials.gov/study/NCT06161181

**International Registered Report Identifier (IRRID):**

DERR1-10.2196/48852

## Introduction

### Adherence to Oral Anticancer Treatments

Metastatic breast cancer (MBC) is an incurable disease, wherein the available medications are primarily focused on deferring disease progression and symptom mitigation, thereby prolonging survival rate as well as preserving the quality of life (QoL) and psychological well-being [1,2]. The clinical advancements achieved in anticancer treatments have increased the survival rates of patients with MBC. The 5-year survival rate of patients with MBC is around 38% [2]. Notwithstanding, several studies [3-6] have shown that adherence to anticancer treatments is a critical issue in the disease trajectory of patients with breast cancer, especially regarding oral anticancer treatments (OATs), which are intensely demanding because patients are responsible for assuming medications according to the medical prescriptions, thereby increasing the risk of not appropriately taking the therapy [7].

From a theoretical perspective and according to the World Health Organization’s recommendations [8], medication adherence might be explained by a set of mutual and interconnected determinants incorporating (1) sociodemographic (eg, age, gender, socioeconomic status), psychocognitive, and social variables (eg, psychological well-being, social support); (2) disease and treatment-related characteristics (eg, cancer stage, prognosis, dosage, side effects); (3) attitudes, beliefs, and values; (4) health literacy and knowledge; and finally (5) health care system–related factors [7,9,10]. Accruing evidence have highlighted that patients with advanced cancer might report significant levels of nonadherence because in case of some cancers such as MBC, the patients have to change the type of treatments or dosage frequently and they experience a high level of fear of cancer spread [3]. For example, Yerrapragada and colleagues [6] reported nonadherence to tamoxifen in patients with MBC, ranging between 30% and 85% and further reducing over time. In addition, patients with MBC reported several barriers to the daily management of OAT, such as emotional (eg, worry, depression) and physical distress related to the side effects (eg, fatigue, weakness, sleep disturbance, emotional burden, pain) and lack of knowledge about their disease. Further, patients might experience a lack of control and a lack of perceived benefits during the disease pathway, and they may experience difficulty in managing therapy [3,6]. Other studies have shown that patients with MBC experience modest QoL due to the related treatment side effects, financial burden affecting therapy discontinuation, and a significant level of nonadherence [4,7]. Marshall and colleagues [4] observed that patients with MBC who frequently report treatment concerns rather than treatment benefits are less likely to be adherent to prescriptions, as well as patients who experience a more significant number and severity of side effects tend to have more medication worries that could negatively impact adherence.

### Risk-Predictive Models and Decision Support Systems

Given the impact of nonadherence on clinical outcomes and the associated economic burden on the health care system [11,12], finding effective ways to increase treatment adherence is particularly relevant. Patients who adopt nonadherent behaviors need support in managing oral therapies and in overcoming individual and systemic barriers and roadblocks [5]. Notwithstanding, the dynamics influencing adherence to OATs are understudied in the cancer field [13], and a comprehensive model of the risk determinants of nonadherence is not currently available, particularly for targeted therapies and novel generations of hormonal therapy [14]. Besides, a shared definition of medication adherence and satisfactory assessment tools is not acknowledged, which vary in terms of accuracy and reliability [14-17], even in the explicit case of the equivalent treatment protocol and diagnosis [13,18]. Because of the direct costs of nonadherence (eg, survival rate, health-related QoL for patients with MBC) and the indirect costs for the health care system (eg, economic burden), it is mandatory to identify potential risk factors of nonadherence to OATs and to define personalized interventions supporting adherence during the clinical pathway in patients with MBC.

Consistently, defining, measuring, and developing a comprehensive model of medication adherence based on real-world data predictive models is a crucial clinical, psychological, social, and economic challenge. Machine learning has become an integral part of the health care industry—from biomedical research to the delivery of health care services. Compared to traditional statistical methods, machine learning provides numerous advantages such as increased flexibility, prediction accuracy, possibility of automation, and processing of big data. Prediction models for adherence have already been developed and tested in various scenarios [19-22]. If adequately reported, these models can help guide treatment decision-making, improve patient outcomes, and streamline perioperative health care management. Considering the complexity of medication nonadherence in patients with MBC, it is critical to identify patients at risk of nonadherence and carry out timely, precise, and tailored interventions to improve their adherence. Through machine learning models, it is possible to provide personalized prediction on medication adherence for a given patient, supporting adherence and performing a specific intervention [22,23].

A growing body of studies have underlined that eHealth technologies (eg, mobile apps, web-based solutions, wearables) might be helpful tools to foster patient management and engagement in clinical decisions during the cancer pathway [24]. Different web-based solutions based on educational and behavioral interventions have been developed for patients with breast cancer to foster medication adherence [25,26]. For example, the Multinational Association for Supportive Care in Cancer has developed an educational and teaching tool for patients with cancer receiving OATs that is composed of different educational sections aimed at assessing general patient knowledge about their treatment protocol and drug information (eg, side effects), skills in the management of therapy, possible strategies to manage nonadherence occurrences, and a specific questionnaire section to evaluate patient comprehension [26]. Moreover, Omaki and colleagues [27] have developed a patient decision aid named “My Healthy Choices” to foster adherence to pain treatments, assessing the environmental and personal risks and setting patient treatment priorities.

Nevertheless, no study has been conducted on patients with MBC to foster medication adherence to OATs through the clinical care pathway based on designing and developing a decision support system (DSS), integrating risk predictive models and educational and training tools. The information embedded in a DSS solution designed and developed according to the needs of patients with MBC might enable users to be better informed, develop more accurate expectations of the benefits and harms, and increase participation in the decision-making processes and medication adherence [28]. Evidence shows that, when implemented on web or mobile apps, DSS may support patients and physicians by improving adherence to medical treatments [27,29,30].

### The Pfizer Project (65080791)

Drawing from the theoretical framework described above, we present and explain the study protocol of a prospective, randomized controlled study that is nested in a large-scale international project named “Enhancing Therapy Adherence Among Metastatic Breast Cancer Patients” (Pfizer 65080791) aimed to develop a predictive model of nonadherence and an associated DSS and guidelines to foster patients’ engagement and therapy adherence among patients with MBC concerning oral chemotherapy, endocrine therapy, supportive care, and the treatment of comorbidities. Consistently, the Pfizer Project (65080791) has been organized into 2 different studies to achieve the key goal. A retrospective study has been designed and a model has been developed to predict adherence to OATs, which use existing physiological, clinical, and QoL data available in the European Institute of Oncology (IEO; Milan, Italy). More in-detail, multimodal retrospective data have been retrieved from patient electronic health records by using natural language processing in a sample of 2750 patients with MBC (from 2010 to 2020). Data included in the analysis have been sociodemographic variables, diagnosis, biochemical and medical tests, procedures and medical history, treatment programs, treatment side effects, comorbidities, and familiarities. Concerning adherence to the treatment protocols, data included the following dimensions: initiation of the treatment, interruption of treatment, and skipped treatment doses. Furthermore, a prospective study is designed to assess the effectiveness of a DSS web-based solution and to enrich the predictive power of the machine learning model to forecast adherence behavior in patients with MBC. The tuning of the model permits adding additional predictors (personality traits, self-efficacy for coping with cancer, sense of coherence, pain, anxiety, depression, risk perception, and QoL) known to influence medication adherence behavior and that are not available retrospectively [10]. These data are used to improve the predictive power of the machine learning model and its capacity to profile patients’ adherence behaviors and to provide an individual risk value of nonadherence.

## Methods

### Primary End Point Analysis

The primary end point was to assess the effectiveness of the DSS web-based solution and the machine learning web application in promoting adherence to OATs in a sample of 100 patients with MBC at 3 months. The adherence is evaluated using the number of pills taken divided by the number of pills prescribed. Further, the adherence is assessed using behavioral measures: the 8-item Morisky Medication Adherence Scale (MMAS-8) [31] and Adherence Attitude Inventory (AAI) [32].

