### Measures

#### Assessment of Nonadherence to OATs

This study uses the operational definition of adherence provided by the International Society for Pharmacoeconomics and Outcomes Research Medication Compliance and Persistence Work Group, which defines adherence as “the extent to which a patient acts in accordance with the prescribed interval and dose of a dosing regimen” [49]. Coherently, the nonadherence to OATs is evaluated using a prospective method [15] by weekly medication diaries and 2 self-reported measures.

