### Calculation of Sample Size

The sample size calculation was based on estimates for the effectiveness of TREAT as the primary outcome, assuming that the final analysis would be performed with a 2-sample 2-sided *t* test, a power of 96.4%, an α of .05, a standard deviation of 1.2, and a minimal difference in outcomes of 0.51 (effect size of 0.42) based on the patients’ self-reported satisfaction with the treatment decision [53]. Under these considerations, the final sample size was calculated to be 100 patients with MBC, with 50 individuals per group (50 patients with MBC exposed to DSS and 50 patients with MBC not exposed to the intervention). This sample size is expanded to 120 when a 20% attrition rate is used.

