#### Propensity Score

For residual confounding after randomization, we will use propensity scores based on inverse probability of treatment weighting [55]. We will first assess the covariate balance between control and intervention groups through standardized mean differences and differences in proportion. Covariates will include the patient demographic and clinical variables. Values greater than 0.1 will signal an imbalance in covariates. Next, we will use inverse probability of treatment weighting generated through logistic regression to balance the covariates [56]. Once we achieve covariate balance, we will estimate the effect for each outcome by using a double robust approach.

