#### Generalized Linear Models

Additional analyses will be run using generalized linear models with a Gaussian distribution family (multiple linear regression) being adjusted for randomization baseline imbalances. These models will evaluate the association between all previously reported outcomes (the number of pills taken during the prescribed interval, MMAS-8, AAI, STAI-Y, BDI-II, CBI-B/I, SOC-13, BPI, EORTC-QLQ-C30, EORTC-QLQ-BR23, BFI, and risk perception) and the intervention (TREAT and machine learning web application), accounting for the baseline differences. We will build one model for each combination of predictor and outcome, where the outcome will be the dependent variable (Y) and the predictor will be the independent variable (X), adjusted for the covariates unbalanced at baseline. We will also evaluate models with a Poisson or negative binomial distribution for non–normally distributed outcomes. Results will be reported as predicted means along with 95% CIs.

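### The primary end point holds three unranked adherence measures with no decision rule, and the t test assumed for the sample size is not reconciled with the weighted doubly robust estimate

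*Protocol article*

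**What the plan says.** **Outcomes.** Primary End Point Analysis fixes the time point ("in a sample of 100 patients with MBC at 3 months") and gives a first measure: "The adherence is evaluated using the number of pills taken divided by the number of pills prescribed". It then adds two questionnaires: "Further, the adherence is assessed using behavioral measures: the 8-item Morisky Medication Adherence Scale (MMAS-8") and the AAI. Assessment of Nonadherence to OATs names the same three sources side by side: nonadherence is evaluated "by weekly medication diaries and 2 self-reported measures". Secondary End Point Analysis lists its own instruments, and neither MMAS-8 nor AAI is among them.

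**Analyses.** Calculation of Sample Size proceeds "assuming that the final analysis would be performed with a 2-sample 2-sided" t test with alpha .05. The difference it uses comes from patients' satisfaction with the treatment decision, which is none of the three adherence measures. Propensity Score says that, once weighting has balanced the covariates, "we will estimate the effect for each outcome by using a double robust approach". Generalized Linear Models begins: "Additional analyses will be run using generalized linear models". It adjusts for covariates found unbalanced at baseline, allows Poisson or negative binomial alternatives, and describes the adherence outcome as a count of pills taken rather than a ratio.

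**The concern.** The text does not say which of the three measures decides effectiveness, or whether one, all or a particular one must be positive. The sample size section provides for a single test at 5%, but three tests are available under the primary heading and at least two analyses could supply the deciding p value.

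Two things are at stake. First, a claim of effectiveness could be made at more than the nominal 5% error without departing from the plan as written. Second, the measures capture different things: doses taken, self-reported medication behaviour, and attitude. If they disagree, the plan gives no answer to its primary question.

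**Working it through.** **1. Rank of the measures.** The sections, set side by side:
- Primary End Point Analysis: pill ratio first, then MMAS-8 and AAI, joined by a word that adds but does not rank.
- Secondary End Point Analysis: MMAS-8 and AAI are absent, so the primary end point is the only one they serve.
- Assessment of Nonadherence to OATs: all three are level.
- Calculation of Sample Size: based on a fourth outcome, so it does not reveal the lead.

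**2. Rank of the analyses.** The t test is the assumed final analysis in the sample size section. The doubly robust estimate is to be made for each outcome. The generalized linear models are called additional. The unreconciled pair is therefore the t test and the weighted estimate.

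**3. The plan's own error figure.** The article gives no error rate for the set of measures. Its only figure is alpha = .05 for one test.

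**4. Three measures, one analysis, any positive result counting.** If the tests are independent: 1 − 0.95³ = 1 − 0.857 = 14.3%.

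The article gives no correlation between the measures, so I assume a common value and show the range (three equicorrelated two-sided z tests, 1,000,000 draws):

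| Correlation | Chance of at least one false positive |
|---|---|
| 0 | 14.3% |
| 0.3 | 13.6% |
| 0.5 | 12.5% |
| 0.7 | 10.9% |
| 0.9 | 8.4% |

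**5. Choice of analysis as well.** I simulated trials with no effect: 50 per group, eight baseline covariates explaining an assumed 10% or 30% of outcome variance, 4,000 trials per scenario. Three analyses were run: t test, regression on covariates with a standardized difference above 0.1, and weighted doubly robust regression.
- One measure, best of three analyses: about 7–8%.
- Three measures, best of three analyses: about 22–23% at correlation 0, 18–20% at 0.5, and 15–17% at 0.7.

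The Monte Carlo standard error near 20% is √(0.2 × 0.8 / 4000) = 0.6 percentage points. These runs include the additional regression models. Choosing only between the t test and the weighted estimate cannot give more than this.

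**6. Remedies compared.**
- One measure and one analysis at .05: 5%.
- All three measures at 0.05/3 with one analysis: at most 5% (1 − (1 − 0.05/3)³ = 4.9% if independent).

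The second route costs power. With the article's difference 0.51 and SD 1.2, d = 0.51/1.2 = 0.425. With 50 per group, d/√(2/50) = 0.425/0.2 = 2.125. Normal-approximation power at alpha .05 is Φ(2.125 − 1.960) = 56.6%. At .05/3 it is Φ(2.125 − 2.394) = 39.4%. The stated 96.4% does not reproduce from these inputs. That is a separate point, but it means there is little power to give up.

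**The case against.** The strongest reply is that the pill ratio is the natural lead. It comes first, it fits the cited definition of adherence (following the prescribed interval and dose), and the limitations section defends the diary as the more accurate method. The generalized linear models are labelled additional, and the weighting has a stated purpose, residual confounding. The article is condensed, so test order and sensitivity labels may stand in an analysis plan that is not shown.

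Much of this limits the point. Four stronger readings should not be drawn:
- **That 14% is a minimum.** It is the independence figure. The three measures target the same behaviour in the same patients, so positive correlation is likely and 14.3% is close to a ceiling for the measures alone.
- **That the four AAI subscales are further primary tests**, giving 1 − 0.95⁶ = 26.5%. The article describes the subscales but plans no primary test on them.
- **That three analyses compete on equal terms.** The models labelled additional rank below something; the conflict is between the other two.
- **That any one positive measure suffices.** The article does not say so. If all three had to be positive, there would be no inflation.

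The rest does not remove the defect. A leaning towards the pill ratio is not a rule, and the sections on assessment and secondary end points point the other way. Naming the primary outcome belongs in the protocol. The two analyses are not left out for a later document: both are stated here, and they disagree.

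**Conclusion.** The point holds. Three unranked measures share the primary end point with no decision rule or multiplicity control, and the t test is not reconciled with the weighted doubly robust estimate.

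If any positive measure counted as success, the false positive rate would be about 8–14% with one analysis, for assumed correlations from 0.9 down to 0. Free choice of analysis as well would raise it to about 15–23% for correlations from 0.7 down to 0, given the assumed covariate strength and all three analyses in play. These figures depend on a success rule that the text neither states nor excludes. The absence of an answer when the measures disagree does not depend on it. The plan should be changed, at little cost.

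**What to change.** - **Primary End Point Analysis:** name the 3-month pill ratio (taken over prescribed) as the sole primary outcome, tested once at two-sided .05 with one prespecified analysis. An example is a linear model of the ratio on arm, with baseline covariates fixed in advance rather than selected by observed imbalance. Baseline MMAS-8 is a candidate because it is collected at T0. A baseline pill ratio is not, because Timeline describes no diary at T0.
- **Secondary outcomes:** MMAS-8, then total AAI.
- **Statistical Considerations:** label the unadjusted t test, the weighted doubly robust estimate and the other generalized linear models as sensitivity analyses.
- **Generalized Linear Models:** replace the count of pills with the ratio, so that the outcome matches its definition.
- **Calculation of Sample Size:** state that the calculation rests on satisfaction with the treatment decision and not on the primary outcome.

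These are changes of wording and need no added patients or data. There are two costs. A positive MMAS-8 or AAI result alone can no longer support an effectiveness claim. The text will also show openly that the trial was not sized on its primary outcome.
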